### Model training and validation

Participants will be randomised in a 3:1 ratio with varying permuted blocks, balanced by cancer ToO and stage, into a model training (75% of participants) or model validation (25% of participants) set. The randomisation list will be pregenerated by a statistician at SCTU. Those in the model training set will have their cohort (cancer case, symptomatic control and asymptomatic control), age and sex shared with PD to train machine learning algorithms in combination with amino acid concentrations. PD will be blinded to the diagnostic status of participants in the model validation set.

Symptomatic controls and healthy volunteers may later be diagnosed with cancer (and therefore move into the cancer cases cohort). Randomisation will therefore only occur on three occasions during the study to reduce the impact of imbalance between building and validation sets. All participants and care providers will remain blinded. Participants will not be randomised more than once. The occasions are as follows: (1) when the amino acid concentrations have been measured for the first batch of 20 participants’ samples with complete data (to stress test processes). (2) When the T_1_ visit has occurred for 50% of the target participants in the breast, colorectal, prostate and lung cancer cohorts. (3) When the T_1_ visit has occurred for all participants, and all data have been returned.

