### Machine learning training and validation

Machine learning techniques considered will include: random forests, support vector machines, ensemble subspace discriminant classifiers, XGBoost, neural networks and deep learning algorithms. The final modelling strategy will be informed by comparative predictive performance and computational cost. Triplicate values of the five amino acids (Cysteine, Reduced Cysteine, Lysine, Tryptophan and Tyrosine) will be used as input parameters (or combined as average readings), with potential additions of participant age and sex. Feature importance will be measured by Shapley values. Stratified cross-validation will be used to reduce overfitting.

One algorithm will predict diagnostic status (‘cancer’ or ‘no cancer’), a second will predict cancer ToO (bladder, breast, colorectal, lung, melanoma, oesophageal, ovarian, pancreatic, prostate and renal) and a third will predict cancer stage (I, II, III, IV). The trained algorithms will use amino acid concentrations (and potentially age and sex) to predict diagnostic status, ToO and cancer stage in the development and validation cohorts. These predictions will be provided to statisticians at SCTU to independently validate predictions against true status.

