### Analysis plan

Baseline medical history, concomitant medications, demographics and Index of Multiple Deprivation will be summarised using descriptive statistics by cohort. The number of symptomatic controls and healthy volunteers who are later diagnosed with cancer and moved into the cancer cases cohort will be presented.

PD will train machine learning algorithms for diagnostic status, ToO and cancer stage. The output for diagnostic status will be a continuous risk score. The output for ToO will be one of the 10 cancers involved in the study, and may include the percentage chance for each ToO. The output for cancer stage will be either stage I, stage II, stage III or stage IV, and may include the percentage chance for each stage. Statisticians at SCTU will produce an AUROC plot in the model training and validation groups for diagnostic status. The apparent c-statistic will be calculated and adjusted for optimism using bootstrapping^16^ with accompanying 95% CIs. Sensitivity will be calculated in each group at cut-offs of 95%, 99% and 99.9% specificity with accompanying 95% CIs. Accuracy of the ToO and cancer stage predictions will be calculated in the model training and validation groups with accompanying 95% CIs.

These analyses will be repeated, stratified by early stage (stage I or II) and late stage (stage III or IV) cancer; ToO; symptomatic controls and healthy volunteers; age band at recruitment; biological sex at birth; availability of screening programme for cancer (screening test available (breast, cervical, colorectal and lung) or not available). All analyses will be conducted in R V.4.4.2 (or higher) or STATA V.17 (or higher).

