## Discussion

This study will determine the diagnostic accuracy of machine learning techniques using the Enlighten test to detect cancer. This will be achieved by running the assay in a group of recently diagnosed cancer patients, patients who are symptomatic but cancer was ruled out, and participants with no symptoms or cancer diagnosis. Utility in guiding cancer diagnosis will also be assessed by determining the accuracy of the predicted ToO and stage of cancer. Cancer diagnosis will be collected and updated via local EHRs across five secondary care sites in the south of England. The potential applicability of the machine learning algorithms in future research will be assessed through a held-out dataset.

While this study focuses on 10 sites of cancer (bladder, breast, colorectal, lung, melanoma, oesophageal, ovarian, pancreatic, prostate and renal), additional ToO may be added, which will require model retraining in future research. This will reduce the risk of false results where a tested individual has a cancer that is not covered by the algorithm, which can delay the time to diagnosis. To improve the proportion of cancers detected early, a substantial number of cancer patients diagnosed at stage I or II must be recruited into the study. The research team have reviewed the throughput of recruitment sites in previous years, and recruitment will be monitored and potentially tailored to ensure that these requirements are met.

Theoretically, amino acids will improve the sensitivity for MCEDs to detect early-stage cancers in comparison to the more commonly used cfDNA and ctDNA techniques. If the Enlighten test does perform in this regard, then it could be used as a triage tool prior to expensive diagnostic imaging for individuals suspected of cancer. A reliable rule-in tool for cancer detection would reduce the overall demand for diagnostic imaging. This would, in turn, allow for individuals with a lower pretest probability of cancer to be tested, therefore increasing the rate of cancers detected early.

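### Tissue-of-origin accuracy is to support a statement on utility, but the article sets no reference for what sex and age alone achieve; with ten equal groups, sex alone scores 20%

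*Protocol article*

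**What the plan says.** The Analysis plan names the measure and its interval: "Accuracy of the ToO and cancer stage predictions will be calculated in the model training and validation groups with accompanying 95% CIs". It describes the prediction as a choice among ten classes: "The output for ToO will be one of the 10 cancers involved in the study". The Discussion says what the measure is for: "Utility in guiding cancer diagnosis will also be assessed by determining the accuracy of the predicted ToO and stage of cancer".

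On inputs, Machine learning training and validation says: "The trained algorithms will use amino acid concentrations (and potentially age and sex) to predict diagnostic status, ToO and cancer stage". Under Model training and validation, participants in the training set have their "age and sex shared with PD to train machine learning algorithms in combination with amino acid concentrations". Sex is therefore available to the developer and may enter the ToO model, but this is not certain.

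The Analysis plan also provides breakdowns: "These analyses will be repeated, stratified by early stage (stage I or II) and late stage (stage III or IV) cancer; ToO", and further by "age band at recruitment; biological sex at birth; availability of screening programme for cancer". Machine learning training and validation adds Shapley values for feature importance. The article names no reference level, null model or comparator for ToO accuracy.

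**The concern.** Accuracy in a ten-class problem has a meaning only against what could be scored without the test. Here that level is not the 10% that ten classes suggest. Prostate and ovarian cancer are fixed by sex and breast cancer nearly so, and sex is known before any blood is drawn. If sex or age is in the model, part of the reported accuracy is owed to them and not to the amino acids. The planned CI describes sampling error around the accuracy; it does not describe the gain over what is already known.

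At stake is the utility statement. An accuracy clearly above one in ten could be read as showing that the assay locates the cancer, when much or all of it might come from sex.

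**Working it through.** **Plan's own figure.** The article states no expected or required ToO accuracy, so there is none to reproduce. Its sample size calculation concerns the cancer/no cancer model. The one figure needed is the number of validation cases: 1000 cases × 25% = 250, as stated under Sample size calculation. Randomisation is balanced by ToO, so the validation shares should follow the overall shares.

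**Assumptions.** The article refers to "50% of the target participants in the breast, colorectal, prostate and lung cancer cohorts" but gives no numbers per cancer. I take all breast cases as female, and let breast, colorectal, prostate and lung each have share *k*, with the other six cancers sharing the rest equally.

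**Sex-only rule.** Name breast for every woman and prostate for every man. Every breast and prostate case is then correct and every other case wrong, so accuracy = breast share + prostate share = 2*k*.

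| Share *k* | Sex-only accuracy 2*k* | Largest class, sex not used |
|---|---|---|
| 10% (all ten equal) | 20% | 10% |
| 12.5% | 25% | 12.5% |
| 15% | 30% | 15% |
| 17.5% | 35% | 17.5% |

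Only the first row follows from equal groups; the other rows are illustrations.

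**Interval in 250 cases (exact Clopper-Pearson).** 50/250 gives 15.2% to 25.5%; 75/250 gives 24.4% to 36.1%. Both exclude 10% with no assay information.

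**Correct calls needed to exceed a fixed reference** (one-sided binomial, 2.5%, n = 250):
- reference 10%: 36 (14.4%)
- reference 20%: 64 (25.6%)
- reference 30%: 90 (36.0%)
- reference 35%: 103 (41.2%)

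An observed accuracy between 14.4% and 25.6% would thus clear 10% without clearing the equal-groups sex-only level.

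**Do the planned breakdowns settle it?**
- *By ToO.* The sex-only rule would show about 100% for breast and prostate and 0% for the other eight, so it would be seen. A model that used age and sex less crudely and spread its calls would not show this pattern, and the breakdown would not give the part due to the amino acids.
- *By sex.* With equal groups and the seven non-sex-specific cancers split 1:1, there are 100 + 350 = 450 men, and always naming prostate scores 100/450 = 22.2%. There are 100 + 100 + 350 = 550 women, and always naming breast scores 100/550 = 18.2%. Over *k* from 10% to 17.5% and 40% to 70% men in the non-sex-specific cancers, the ranges are about 17% to 42% in men and 16% to 43% in women. A single-sex stratum therefore still needs a reference.
- *Shapley values.* They describe how a fitted model uses its inputs. They give no validated difference in accuracy and no CI.

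**Would macro-averaging help?** The mean of the ten per-cancer accuracies under the sex-only rule is (1 + 1 + 8 × 0)/10 = 20% whatever the mix. It steadies the figure for this rule but leaves the reference problem in place.

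**The case against.** The best reply is that the article never claims ToO accuracy is to be read against 10%, sets no threshold for it and plans no test; ToO prediction is a secondary aim in a study that defers clinical use to further research. The breakdowns by ToO and sex, with Shapley values, already offer ways to see whether sex drives the result. Sex is only a possible input. A comparator may also stand in the full protocol or the analysis plan, neither of which is shown.

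Much of this stands. It limits the point to an improvement of the stated method, and no error or contradiction is alleged. What remains is that the article does fix the measure and does tie utility to it, and none of the planned outputs gives the validated gain from the amino acids.

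Three stronger readings are tempting and are not supported:
- *That a single overall accuracy is all that will be reported.* The Analysis plan repeats the analyses by ToO and by sex.
- *That the level without the assay is 35%.* This needs breast and prostate together to be 35% of cases, a mix the article does not give.
- *That recruitment will be tailored in a way that shifts the cancer mix.* The tailoring in the Discussion concerns recruiting enough stage I or II patients; any effect on the ToO mix would be indirect.

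**Conclusion.** The point holds as a worthwhile, inexpensive improvement. Raw ToO accuracy, even with its CI and breakdowns, cannot show what the assay adds when age and sex may be in the model and several of the ten classes depend on sex. With equal groups and breast taken as all female, sex alone scores 20%, twice the one-in-ten level. Figures of 25% to 35% depend on assumed shares of 12.5% to 17.5% each for breast and prostate. If sex is not an input, the trivial reference is the largest class share: 10% with equal groups, up to 17.5% under the same assumptions. My confidence is moderate, because the inputs to the final ToO model are still open and a reference may be specified in documents not shown.

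**What to change.** In the Analysis plan, add for the validation set the paired difference in ToO accuracy, with a bootstrap 95% CI, between (i) a model using amino acids plus age and sex and (ii) a model using age and sex only. Train both on the same training set and resample validation cases so that each case keeps both predictions. In the Discussion, base the statement on utility on this gain as well as on raw accuracy.

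If the final ToO model excludes age and sex, the two models are not nested and their difference is not the gain from the amino acids. In that case, report the model's accuracy next to that of the age-and-sex-only model and the largest class share.

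The interval is for estimation. I do not propose a rule that utility may be claimed only if it excludes zero; such a test would be debatable for a descriptive secondary aim.

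Cost: one small extra model on data already collected, a few lines of text and no additional participants. The downside is that the ToO result may look less favourable.

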### Ethics and dissemination

This study is sponsored by University Hospitals Southampton NHS Foundation Trust and has been approved by the Health Research Authority and Health and Care Research West Midlands (24/WM/0234). This study is funded jointly by the National Institute for Health Research and the Office for Life Sciences (ref NIHR207538). SCTU is committed to the responsible sharing of clinical study data and samples with the wider research community. Data and sample access are administered through the SCTU Data and Sample Release Committee, which will consider requests once the final analysis has been published.

Results will be presented at scientific meetings and published in international peer-reviewed journals. Lay summaries of study progress and findings will be published on SCTU’s website.

### Patient and public involvement

This study benefits from two funded PPI coapplicants who have lived experience of cancer, have extensive experience in providing a patient’s perspective in cancer research and an interest in equality, diversity and inclusion. They have contributed to the conception and development of the study and will be advising on the content and tone of patient-facing materials. They will also lead the public dissemination strategy and participate in all regular study management group meetings.

## Discussion

This study will determine the diagnostic accuracy of machine learning techniques using the Enlighten test to detect cancer. This will be achieved by running the assay in a group of recently diagnosed cancer patients, patients who are symptomatic but cancer was ruled out, and participants with no symptoms or cancer diagnosis. Utility in guiding cancer diagnosis will also be assessed by determining the accuracy of the predicted ToO and stage of cancer. Cancer diagnosis will be collected and updated via local EHRs across five secondary care sites in the south of England. The potential applicability of the machine learning algorithms in future research will be assessed through a held-out dataset.

While this study focuses on 10 sites of cancer (bladder, breast, colorectal, lung, melanoma, oesophageal, ovarian, pancreatic, prostate and renal), additional ToO may be added, which will require model retraining in future research. This will reduce the risk of false results where a tested individual has a cancer that is not covered by the algorithm, which can delay the time to diagnosis. To improve the proportion of cancers detected early, a substantial number of cancer patients diagnosed at stage I or II must be recruited into the study. The research team have reviewed the throughput of recruitment sites in previous years, and recruitment will be monitored and potentially tailored to ensure that these requirements are met.

Theoretically, amino acids will improve the sensitivity for MCEDs to detect early-stage cancers in comparison to the more commonly used cfDNA and ctDNA techniques. If the Enlighten test does perform in this regard, then it could be used as a triage tool prior to expensive diagnostic imaging for individuals suspected of cancer. A reliable rule-in tool for cancer detection would reduce the overall demand for diagnostic imaging. This would, in turn, allow for individuals with a lower pretest probability of cancer to be tested, therefore increasing the rate of cancers detected early.

If the results from this study are promising, then the aim of future research will be to demonstrate an improvement in early-stage cancer detection balanced against the harms of overdiagnosis and cost in a randomised controlled trial. The feasibility of progressing to this stage depends on the recruitment success for all combinations of cancer ToO and stages, and the clinical acceptability of a 10 cancer MCED versus developing the MCED across further cancer ToO.
